## Methods

### Study design

SPARKLE is a post-authorization safety and efficacy registry in Europe, designed as a multicenter, international, prospective cohort study of patients with alpha-mannosidosis (Fig. 1). The primary objective is to assess the long-term effectiveness and safety of treatment with velmanase alfa under conditions of routine clinical care; secondary objectives include expanding the current understanding of alpha-mannosidosis by collecting data to characterize the natural history of the disease. Source data will be collected by the investigator in the patient file and captured in an electronic case report form (eCRF). This also includes data from patients receiving treatment in a home-care setting. The study, which started patient enrollment in 2020, has an indefinite recruitment period. Patients will be followed for up to 15 years after inclusion. The end of the study is defined as the last visit of the last patient registered in the study. The study will be conducted under conditions of routine clinical practice, according to the treating physician, without mandatory registry assessments. Patients are eligible for the study irrespective of treatment (velmanase alfa, hematopoietic stem cell transplantation or any biologic substance received as part of a clinical trial during participation in the registry).

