^d^Patients’ retrospective data may be collected at the time of registry enrolment if available. Baseline visits are recommended to be repeated for those patients who will start VA therapy during the course of the study, before therapy is initiated

^e^Physical examination to collect vital signs, anthropometric measurements like height, weight, rate of growth, and the ability to perform the endurance test at the study visit

^f^If applicable, information regarding weekly VA therapy received by the patient need to be recorded within all the registry duration

^g^All assessments mentioned in the above table will be collected only if considered necessary and available as part of routine clinical practice by the treating physician; no additional tests specific to the registry will be done

^h^Standard test for hematology assessed by local laboratory if available per clinical practice of the site: hemoglobin, hematocrit, platelet count, red blood cells, and white blood cells with differential count (all expressed in %, as well as in absolute numbers)

^i^Standard test for hematology assessed by local laboratory if available per clinical practice: serum electrolytes, creatinine, creatine-kinase, amylase, AST, ALT, ALP, albumin, bilirubin (total and direct), LDH

^j^The markers (oligosaccharides in serum, IgG, IgA, and ADA) will be evaluated through a central laboratory in European countries other than Germany. In Germany, marker testing will take place according to local routine clinical practice

^k^In patients 4 years and older, and when applicable according to the judgment of treating physician

^l^In patients under 4 years of age and when applicable according to the judgment of treating physician

^m^AEs/ADRs based on all risk categories associated with VA European RMP, including infusion-related reactions and hypersensitivity (as identified risks), acute renal failure, loss of consciousness and medication errors (as potential risks). Data on pregnancy (including birth and newborn data) and lactation (as missing information) will be also collected if available

^n^One of the behavior checklists (CBCL pre-scholar/scholar, ABCL/ASR [self-reporting], OABCL) will be used to the applicable age and according to the judgment of treating physician

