### Effectiveness variables

Efficacy outcomes to be assessed during routine clinical care are shown in Table 1. For patients under 4 years of age, a 3-min stair climb test (3MSCT) and 2-min walk test (2MWT) are suggested. The forced vital capacity (% volume predicted) is suggested for patients over 4 years of age, and according to the judgment of the treating physician. The proposed schedule of assessments is shown in Table 2, but, again, assessments will be made based on the participating centers’ Standard Operating Procedures.

A global treatment response (GTR) to velmanase alfa will be evaluated in velmanase alfa-naïve patients able to perform the functional tests after 3 years of treatment. The GTR will assess patients in three clinical domains (pharmacodynamic, functional, and QoL) consisting of 1 or > 1 endpoint (Table 3). The pharmacodynamic domain comprises a measure of the accumulated substrate in alpha-mannosidase deficiency, the main pathogenic factor for disease manifestations; a decrease in oligosaccharides is a key biomarker of the pharmacologic effect of the ERT [4]. The second domain includes pulmonary function, endurance, and fine and gross motor proficiency, i.e., all the functional endpoints of the disease [4]. The QoL domain relates to patient-related outcomes of disease burden, disability, and pain [4]. A global response is defined as improvements exceeding the established minimal clinical important difference (MCID) (Table 3) in ≥ 1 endpoint in ≥ 2 of the domains [4]. The MCIDs are derived on the basis of those used in clinical conditions with the highest similarity to alpha-mannosidosis (proxy diseases) [14–17]. Collection of the same effectiveness variables is suggested for patients who are not treated with velmanase alfa, in order to support the description of the natural course of the disease.

**Table 3 Tab3:** Clinical domains, endpoints, and MCID thresholds for the GTR

Domain	Endpoint	Established MCID^a^
Pharmacodynamic	Serum oligosaccharides	Last serum oligosaccharide value ≤ 4 µmol/L
Functional	3MSCT	Improvement ≥ 7 steps/min [14]
	6MWT	Improvement ≥ 30 m [16]
	FVC%	Improvement ≥ 10% [15]
Quality of life	CHAQ DI	Improvement ≤ –0.130 [17]
	CHAQ Pain VAS	Improvement ≤ –0.246 [17]

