### Statistical analyses

Baseline demographic and disease characteristics will be presented by means of descriptive statistics and frequency distributions, as appropriate. Descriptive safety outcomes will be presented and summarized over time. For AEs, both the frequency of patients with an AE and the number of events will be presented by year from baseline. Safety variables will be presented based on person-years at risk. Effectiveness variables will be summarized by means of descriptive statistics or frequency of distribution, as appropriate, and all variables (actual values and change from baseline, if applicable) will be presented by time point. The effects of baseline characteristics on effectiveness will be evaluated by means of regression/logistic models. Covariates in the model will be age (< 18 and ≥ 18 years), sex (male, female), sibships, genotype (Groups 1, 2, and 3, per Borgwardt et al.) [18], residual enzymatic activity (< 10, 10 to < 15, and ≥ 15 nmol/h/mg), and Childhood Health Assessment Questionnaire Disability Index (0–1, 1–2, and 2–3).

Provided that a sufficient number of nontreated patients with adequate data are enrolled, a comparison will be conducted between the velmanase alfa-treated and nontreated groups. Propensity score (PS) analysis will be used to compare GTRs after 3 years; the PS will be calculated as the predicted probability of response using logistic regression, with the same covariates as used for the baseline characteristics regression. Subgroup analyses may be performed depending on overall sample size; results will be presented descriptively.

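### A patient's chance of being classed a global responder rises with the number and spread of endpoints measured, and the planned treated-versus-nontreated comparison does not control for this

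*Protocol article*

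**What the plan says.** In the protocol article, Effectiveness variables, global treatment response (GTR) is assessed in "three clinical domains (pharmacodynamic, functional, and QoL) consisting of 1 or > 1 endpoint". The definition reads: "A global response is defined as improvements exceeding the established minimal clinical important difference (MCID") "in ≥ 1 endpoint in ≥ 2 of the domains". Table 3 gives serum oligosaccharides for the pharmacodynamic domain, 3MSCT, 6MWT and FVC% for the functional domain, and CHAQ DI and CHAQ Pain VAS for quality of life. GTR is evaluated after 3 years in treatment-naïve patients who are able to perform the functional tests.

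Study design states that the registry runs "without mandatory registry assessments". Footnote g of Table 2 says the listed assessments "will be collected only if considered necessary and available as part of routine clinical practice by the treating physician". Effectiveness variables adds that "assessments will be made based on the participating centers’ Standard Operating Procedures".

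Statistical analyses then plans a group comparison: "Propensity score (PS) analysis will be used to compare GTRs after 3 years". The propensity score uses the covariates of the baseline regression: age, sex, sibships, genotype, residual enzymatic activity and CHAQ DI. The comparison is conditional on enough nontreated patients having adequate data, a term the article does not define.

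**The concern.** The response rule rewards testing. Within a domain, any one endpoint over its threshold is enough, so each further endpoint measured is another chance to meet that domain. Across domains, two of three are needed, so a patient measured in only one domain cannot be a responder. Being able to perform a functional test does not mean that it was performed. Every endpoint except oligosaccharides is a change, so it needs a baseline value as well as a follow-up value.

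Two results are exposed. The single-arm GTR mixes benefit with local testing practice. The treated-versus-nontreated comparison can show a difference with no clinical difference behind it if one group is measured more completely. Neither site nor testing completeness is among the listed covariates. The number of tests available at 3 years is not a baseline characteristic, so the propensity score could remove only the part of the imbalance that those covariates happen to predict.

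**Working it through.** **The plan's own figure.** Table 4 gives Clopper–Pearson limits for 70 treated patients. At a GTR of 0.60 (42 of 70) the two-sided 95% limits recompute to 0.476 and 0.715, as printed. The other four rows also reproduce.

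**Inputs from the article.** Domains hold 1, 3 and 2 endpoints, and response needs at least two domains met (Effectiveness variables, Table 3).

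**Inputs assumed, not in the article.** Endpoints are independent. The chance of crossing the threshold is e = 0.20 for each functional or quality-of-life endpoint (range 0.15 to 0.30) and p = 0.70 for oligosaccharides. An unmeasured endpoint cannot count as met. The same p and e apply to everyone, so any gap comes from testing alone.

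**Formulas.** With k endpoints measured in a domain, P(domain met) = 1 − (1 − e)^k. With f for functional and q for quality of life, P(GTR) = pf + pq + fq − 2pfq.

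**Main contrast at e = 0.20.** CHAQ DI and Pain VAS both belong to the CHAQ, a single row in Table 2, so a site using it would ordinarily have both: q = 1 − 0.8² = 0.36.
- All six endpoints: f = 1 − 0.8³ = 0.488. P = 0.3416 + 0.2520 + 0.1757 − 2(0.1230) = 0.523.
- Two functional tests plus CHAQ: f = 0.36. P = 0.2520 + 0.2520 + 0.1296 − 2(0.0907) = 0.452.
- One functional test plus CHAQ: f = 0.20. P = 0.1400 + 0.2520 + 0.0720 − 2(0.0504) = 0.363.

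**Range.** Six endpoints versus one functional test plus CHAQ:
- e = 0.15: 0.42 vs 0.28
- e = 0.20: 0.52 vs 0.36
- e = 0.30: 0.68 vs 0.51

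**Spread as well as number.** At e = 0.20, five endpoints without oligosaccharides give fq = 0.488 × 0.36 = 0.18. Four endpoints without CHAQ give pf = 0.70 × 0.488 = 0.34. Four endpoints over all three domains (one functional test plus CHAQ) give 0.36. A count of tests alone therefore does not determine the rate.

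**Correlation.** This was checked for a wider contrast, all six endpoints versus one per domain, with 0.30 for every endpoint. Independence gives 0.484 vs 0.216. Correlations of 0.3, 0.5 and 0.7 give 0.444 vs 0.251, 0.418 vs 0.268 and 0.390 vs 0.283. The gap shrinks but stays.

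**Single-arm rate.** A common endpoint probability of 0.36 gives GTR 0.60 when all six are measured. If each endpoint is measured with probability 0.9, independently, the effective probability is 0.324 and GTR is 0.53 (lower limit at n = 70: 0.409). With 0.8 it is 0.288 and GTR is 0.46 (lower limit 0.340). Both limits fall below the 45.0% in Study size with no change in true benefit, provided that unmeasured endpoints count as not met.

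**The case against.** A reader might infer that one endpoint over threshold makes a responder. It does not: two domains must be met, which is stricter.

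A reader might also infer that the rule favours velmanase alfa because treated patients are tested more. The article does not show that. All six endpoints carry the same baseline and yearly marks in Table 2 for every patient. The six-month column, highly recommended for recent starters, contains none of the six. The unscheduled column, worded for treatment starters, contains oligosaccharides and FVC but not 3MSCT, 6MWT or CHAQ, and its example timing is 3 months, not 3 years. Effectiveness variables suggests collecting the same variables in untreated patients. Heavier testing of treated patients is plausible, but the direction of any bias stays conditional.

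The adequate-data condition on nontreated patients is a partial safeguard. As written, it is undefined and is not applied to the treated group.

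Rules for evaluability and missing components are commonly left to the full protocol or analysis plan, and such a rule may exist there. Requiring or imputing every endpoint would remove the dependence. An evaluability rule that only sets a minimum per domain would not: in the 52% versus 36% contrast, all three domains are measured in both cases.

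Finally, there is no formal hypothesis test, the discussion admits that assessments vary between centres, and incomplete testing would lower the single-arm GTR rather than flatter the drug. These points limit the severity. They do not remove the mechanism, which the discussion does not connect to GTR.

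**Conclusion.** The concern stands in conditional form, as a should-fix. The article itself combines a response rule that accepts any endpoint within a domain, optional testing, and a group comparison whose listed covariates say nothing about testing. Followed as written, the chance of response rises with the number and spread of endpoints measured.

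The size is illustrative: about 16 percentage points (52% vs 36%) between full testing and one functional test plus CHAQ, and 14 to 17 points over the range shown. It rests on assumed endpoint probabilities, independence, and no credit for unmeasured endpoints. No separate oligosaccharide probability was set for nontreated patients, so these figures do not estimate the bias in the actual comparison. That bias arises only if completeness differs between groups, and its sign follows whichever group is measured more fully.

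**What to change.** Keep GTR as defined as the outcome. For the treated-versus-nontreated comparison:
- Add an analysis that scores both groups on the same prespecified endpoint set, with the same endpoints required in every patient compared.
- Define the data-adequacy condition and apply it to both groups.
- Report, by group, how many patients lack enough measured domains, with a sensitivity rate that counts them as non-responders.
- Tabulate GTR by endpoints and domains measured. The same table for the treated patients alone would show how far the single-arm rate depends on testing.

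If the full protocol or analysis plan already holds such rules, confirming them would suffice for those items.

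The cost is some wording and one or two extra tables. No tests are added, so the registry remains non-interventional. The downside is a smaller denominator in the common-endpoint analysis. Patients with complete data may also differ from the rest, which is why the sensitivity rate should accompany it.

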### Patient population

Any patient in the European Union with a genetic confirmed diagnosis of alpha-mannosidosis who is willing to participate will be eligible for inclusion. Inclusion criteria are limited to a signed and dated informed consent form, including agreement to permit the Investigator to enter assessment data in the registry that has been recorded prior to inclusion in the registry, which has been obtained from the patient’s medical record. The inclusion form is signed by the patient, parents or a legally acceptable representative according to local regulation. There are no exclusion criteria for patients with this disease. Alpha-mannosidosis and its treatment will progress over the duration of the study and the study protocol may be amended as necessary. Patients’ informed consent will be required for any substantial changes.

Populations for analysis include a velmanase alfa and a no-velmanase alfa safety and efficacy analysis set. The velmanase alfa safety analysis set includes all patients in the registry who have, at some time, received any study drug treatment with a minimum individual follow-up of ≥ 1 month after the last dose. The velmanase alfa efficacy analysis set consists of patients in the same safety analysis set with efficacy evaluations during velmanase alfa treatment and for 12 months thereafter. The no-velmanase alfa safety analysis set includes patients only for the time when they are not, and have not within 1 month, been taking velmanase alfa. The no-velmanase alfa efficacy analysis set includes patients only for the time when they are not, and have not within 12 months, been taking velmanase alfa.

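### The pharmacodynamic domain of the global treatment response is scored as an oligosaccharide level with no baseline condition, although the plan defines response as improvement

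*Protocol article*

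**What the plan says.** All of the following is in the protocol article.

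- **Definition of response** (Effectiveness variables): "A global response is defined as improvements exceeding the established minimal clinical important difference", in at least one endpoint in each of at least two domains.
- **Reason for the pharmacodynamic domain** (same section): "a decrease in oligosaccharides is a key biomarker of the pharmacologic effect of the ERT".
- **Population and time** (same section): the GTR is evaluated in "velmanase alfa-naïve patients able to perform the functional tests after 3 years of treatment".
- **Scoring rule** (Table 3): the only pharmacodynamic criterion is a "Last serum oligosaccharide value" of at most 4 µmol/L. The three functional and two quality-of-life criteria are all worded as improvements, for example "Improvement ≥ 7 steps/min" for the stair-climb test. Footnote a names a proxy disease as the source of each of these five thresholds and none for oligosaccharides.
- **Use of the GTR**: Study size bases the planned 70 treated patients on it. Statistical analyses plans a propensity-score comparison of 3-year GTRs between treated and untreated patients, if enough untreated patients with adequate data are enrolled.
- **Eligibility** (Study design, Patient population): there are no exclusion criteria, and patients may enter whatever their treatment, including stem cell transplantation.

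**The concern.** The text describes a change and the table scores a level. The two agree only if every patient starts above 4 µmol/L. A patient who starts at or below that value and stays there satisfies the domain with no change, or even after a rise that remains within the limit.

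Because two of three domains are required, such a patient needs only one further domain, while everyone else must improve in two. In the treated group this can raise the GTR, which is the primary effectiveness outcome. In the comparison with untreated patients, the domain would partly record who had low values at entry. The covariates listed under Statistical analyses include residual enzymatic activity but not baseline oligosaccharides.

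**Working it through.** **1. The six criteria side by side (Table 3)**

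| Domain | Endpoint | Criterion | Needs a change? |
|---|---|---|---|
| Pharmacodynamic | Serum oligosaccharides | last value ≤ 4 µmol/L | No |
| Functional | 3MSCT | gain ≥ 7 steps/min | Yes |
| Functional | 6MWT | gain ≥ 30 m | Yes |
| Functional | FVC% | gain ≥ 10% | Yes |
| Quality of life | CHAQ DI | change ≤ –0.130 | Yes |
| Quality of life | CHAQ Pain VAS | change ≤ –0.246 | Yes |

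Five of six match the definition in the text. The sixth is the sole endpoint of its domain.

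**2. Can low baseline values occur?** Nothing in the eligibility rules prevents them. Being naïve to velmanase alfa does not exclude a patient who was transplanted or who received another biologic in a trial. The documents give no baseline oligosaccharide distribution, so low values are possible but not shown.

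**3. Reproducing Table 4.** With n = 70 and x = 70 × p, the Clopper–Pearson limits are:

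- lower = 2.5% quantile of Beta(x, n − x + 1)
- upper = 97.5% quantile of Beta(x + 1, n − x)

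| p | x | Lower | Upper | Width |
|---|---|---|---|---|
| 0.60 | 42 | 0.476 | 0.715 | 0.239 |
| 0.65 | 45.5 | 0.527 | 0.760 | 0.234 |
| 0.70 | 49 | 0.579 | 0.804 | 0.225 |
| 0.75 | 52.5 | 0.632 | 0.846 | 0.214 |
| 0.80 | 56 | 0.687 | 0.886 | 0.199 |

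All rows match Table 4, so the sample-size arithmetic is sound. The issue is only what counts as a responder.

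**4. Sensitivity to reclassification.** Let k be the number of responders who met the pharmacodynamic domain only because they started at or below 4 µmol/L, and who met exactly one other domain. Under an improvement rule they are no longer responders. The value of k is an assumption.

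| Responders by Table 3 | k | Remaining | Lower limit |
|---|---|---|---|
| 42 | 1 | 41/70 | 0.462 |
| 42 | 2 | 40/70 | 0.447 |
| 42 | 4 | 38/70 | 0.419 |
| 49 | 7 | 42/70 | 0.476 |
| 49 | 10 | 39/70 | 0.433 |
| 56 | 10 | 46/70 | 0.534 |

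At least 41 of 70 responders are needed for a lower limit above 45%.

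**5. From share to GTR, under assumptions.** Let f be the share of patients at or below 4 µmol/L both at baseline and at the last value. Let F and Q be the probabilities of functional and quality-of-life response, taken as independent of each other and of the oligosaccharide value. Automatic credit changes the outcome only when exactly one of these two domains is met, so

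inflation = f × (F + Q − 2FQ).

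- F = Q = 0.5: the factor is 0.50. f = 0.05, 0.10, 0.20 gives 0.025, 0.050, 0.100.
- F = Q = 0.3: the factor is 0.42. The same shares give 0.021, 0.042, 0.084.

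None of f, F or Q is in the documents. The range shows how the rule behaves and is not an estimate.

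**The case against.** The strongest reply is that nothing shows any velmanase alfa-naïve patient starting at or below 4 µmol/L. The article treats accumulated substrate as the main driver of disease, so such patients may be few or absent. The plan also states that it tests no formal hypothesis, so 45% is a reference value and not a decision rule. The comparison with untreated patients is conditional, and crediting untreated patients alone would shrink the difference, not favour the drug. All of this stands. It limits the size, but it does not reconcile the table with the text.

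The level could also be defended as carried over from the model applied post hoc to the pivotal trial. The Background gives that model's two-domain rule but not its oligosaccharide threshold, so the documents do not settle this.

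Three stronger readings are tempting and are not supported:

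- *A low value makes a patient a global responder.* It does not. It credits one domain, and a second is still required.
- *The last value could come from year 10 or from after treatment stopped.* The efficacy set does cover patients "with efficacy evaluations during velmanase alfa treatment and for 12 months thereafter", and follow-up runs to 15 years. But that clause defines an analysis set, whereas the GTR is placed at 3 years of treatment. The last value reads naturally as the last one available at that evaluation. Visit windows may be left to the full protocol or SAP.
- *Testing in another laboratory credits a response.* Outside Germany the marker goes to a central laboratory, and footnote j to Table 2 adds: "In Germany, marker testing will take place according to local routine clinical practice". Differences between laboratories around a fixed cut-off can misclassify in either direction. The Discussion already acknowledges variation between centres.

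**Conclusion.** The point holds as a contradiction between the stated definition of response and the Table 3 rule for one of its three domains. It is a rule that the article states, not a detail left to the SAP. Followed literally, it credits a patient who starts at or below 4 µmol/L, treated or untreated, with one of the two required domains without improvement.

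The size is unknown because the number of such patients is not given. It would matter most near the plan's lowest assumed GTR: at 42 of 70, two reclassified responders (2/70 = 2.9% of the treated group) bring the lower limit below 45%. At 56 of 70 the statement about 45% survives ten. In the comparison with untreated patients, the direction of any bias depends on which group has more low baseline values, and the documents do not show this. The point should be settled before GTR results are analysed, but it does not call the study size or Table 4 into question.

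**What to change.** - **Table 3.** Define pharmacodynamic response as a baseline value above 4 µmol/L (treatment baseline for treated patients) together with a last value, up to the 3-year evaluation, of at most 4 µmol/L. For treated patients this last value should be on treatment. Patients at or below 4 µmol/L at baseline must then respond in both the functional and quality-of-life domains.
- **Untreated patients.** Apply the same rule, with the registry baseline as reference.
- **Sensitivity analyses.** Report the GTR under the present Table 3 rule, and report results by laboratory type (central or local). Keep German local-laboratory values in the primary analysis. Dropping them would remove the whole pharmacodynamic domain for patients tested only locally.
- **Reporting.** Give the number of patients at or below 4 µmol/L at baseline in each group, so that the size of the issue is visible.

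The cost is a change of wording in Table 3 and the SAP. Table 2 already suggests oligosaccharides at baseline and yearly. A few patients may lose automatic credit, and the definition departs slightly from the present Table 3 model. A baseline value also becomes necessary. Since tests are done only where routine care includes them, some patients may lack one, and their handling should be stated in advance.
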